### Withdrawal conditions

The withdrawal conditions will be as follows: the subject has an allergic or serious adverse reaction and, based on the judgment of the physician, the trial should be terminated; if deterioration occurs during the trial and, based on the judgment of the physician, the trial should be terminated; or the guardians of the subject change medicine at their own will or use Chinese or Western drugs prohibited by this trial. Subjects can terminate participation in the trial as follows: subjects who decide to terminate participation in the trial for any reason; subjects or their guardians who are not willing to, or cannot continue the clinical trial, and thereby terminate participation in the trial; and subjects, although not required to terminate participation in the trial, no longer accept the treatment and examinations. The case record forms (CRFs) for the withdrawn cases will be preserved. The results of the last trial will be considered to be the final results. The data on the clinical efficacy and adverse reactions of acupuncture will be fully analyzed.

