#### Dropout cases

For dropout cases, the researchers will specify the reason for dropping out in the CRF. At the same time, the researchers will contact the guardians and complete the assessment items; the causes for dropping out will be made clear and specified in the CRF. The observational data on all dropout cases will be preserved for statistical analysis at the end of the trial.

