### Recruitment strategies

The subjects will be informed of the details regarding the trial plan and those who voluntarily participate in the trial will receive free ophthalmologic examinations. Following optometric evaluation, these subjects will receive the highest discount (30% off) on glasses. Subjects in the experimental group will receive a 50% discount on acupuncture treatment. All subjects who receive a follow-up eye exam will not pay a fee and will be permitted to be fast-tracked. The subjects who will be included in the experimental group will receive treatment any time between 10:00 and 19:00 (Beijing time). If adverse events occur during treatment, the treatment will be immediately terminated, and help will be obtained from the emergency department. According to the specific condition which occurs after treatment, a consultation involving at least three experts will be carried out to decide whether or not to continue the clinical trial. Subject compliance will be determined based on whether or not the subject receives due treatment. The researchers will ensure that the subjects in the experimental group fully understand the importance of regular acupuncture and compliance. During the observation period, the use of drugs or other therapies to treat mild-to-moderate myopia will be prohibited.

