### Statistical analysis

All statistical analyses will be performed using SPSS 17.0 statistics software. For quantitative data, the distribution pattern and homogeneity of variance will be examined. If there is a symmetric distribution, the mean (M) ± standard deviation will be used for statistical description, otherwise the M interquartile range (IQR) will be used to describe the trend of concentration and amount of scatter. If this condition is met, the Student's t-test will be used to compare the differences between the quantitative indices between the groups, otherwise the Wilcoxon rank-sum test will be used. For categorical data (binary classification and multiple classification), the composition ratio will be used for statistical description. Based on the observation of a theoretical frequency distribution, the χ^2^ or Fisher's exact test will be used, depending on the specific situation. The ranked data will be analyzed using the Wilcoxon rank-sum test.

Primary and secondary outcomes will be analyzed by the superiority test in accordance with the principle of intention-to-treat, using Per Protocol Set (PPS) and Full Analysis Set (FAS) datasets. The indices of safety evaluation will be analyzed using the Save Set (SS) dataset. The significance level in this study will be set at α = 0.05, and the one-sided test will be used. The detailed statistical analytical methods for primary and secondary outcomes and baseline data are shown in Table 
2 (variables, measures, and methods of analysis).

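### Prohibited drug use triggers withdrawal from the trial with no stated continuation of the month-3, 5 and 8 examinations, so an earlier value replaces the true later outcome despite the intention-to-treat principle

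*Protocol article*

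**What the plan says.** All references are to the protocol article.

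- **Withdrawal conditions** lists three grounds. An adverse reaction counts if the physician judges so, and deterioration is qualified in the same way: "if deterioration occurs during the trial and, based on the judgment of the physician, the trial should be terminated". The third ground has no such qualifier: "the guardians of the subject change medicine at their own will or use Chinese or Western drugs prohibited by this trial". A separate, voluntary route covers those who "no longer accept the treatment and examinations". For withdrawn cases, "The results of the last trial will be considered to be the final results", and their efficacy and safety data are to be analysed.
- **Recruitment strategies** states the ban more widely than the third ground does: "During the observation period, the use of drugs or other therapies to treat mild-to-moderate myopia will be prohibited".
- **Standards of dropout cases** treats every non-completer as a dropout and names breach of the trial plan and lack of efficacy among the usual causes.
- **Dropout cases** says that "the researchers will contact the guardians and complete the assessment items" and that dropouts' data are kept for analysis.
- **Excluded cases** removes from efficacy analysis only children enrolled in error or not treated.
- **Statistical analysis** promises: "Primary and secondary outcomes will be analyzed by the superiority test in accordance with the principle of intention-to-treat", with a full analysis set and a per-protocol set.
- **Table 1** schedules diopter at baseline and at months 3, 5 and 8, with none during the treatment phase. **Table 2** analyses use of other drugs as a binary variable.

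**The concern.** Starting another drug happens after randomisation. Under intention-to-treat, a child who does so should still be measured on schedule and compared in the allocated group. Here the event ends participation, whether or not the family would keep attending.

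The Discussion explains that there is no sham arm, so families know the allocation. A family whose child has been given lenses only, or whose child is progressing, may be more inclined to look for other treatment. If so, the missing later readings are related to both arm and outcome. The Discussion itself treats loss to follow-up as a source of bias to be prevented, and this rule adds an avoidable loss of measurements.

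The trigger is also narrower than the ban. The withdrawal list names medicines and drugs, while Recruitment strategies also prohibits other therapies. Two breaches of one ban therefore have different written consequences.

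**Working it through.** **1. Is withdrawal required or optional?** The first two grounds depend on the physician's judgment; the third does not. The voluntary route is worded for subjects who are not obliged to leave, so the text separates required from chosen exit. Prohibited drug use falls on the required side.

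**2. Does measurement continue?** Withdrawn children are non-completers and hence dropouts, so the section on dropout cases applies. It asks for completion of the assessment items, but gives neither a number of assessments nor a month. The sentence making the last result final presupposes that no later reading will come. No section keeps these children on months 3, 5 and 8.

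**3. Are they analysed?** Yes. Their data are kept, and prohibited drug use is not a reason for exclusion from efficacy analysis. What changes is the value that enters at month 8. I read the last result as the last available examination, carried forward. Because Table 1 has no diopter reading in the treatment phase, a child withdrawn in the first two months may have only the baseline value, unless completing the assessment items supplies another.

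**4. Size.** The plan gives no figure for this rule. Its nearest figure is the 20% dropout allowance, which reproduces: 79/0.8 = 98.75, so 99, against 100 stated. The 79 itself does not follow from the printed inputs: 2 × [(1.645 + 0.845) × 0.25/(3.0 − 0.2)]² = 0.099, or 1 per arm. That is a separate matter. From the sample size section I use only the 20% as an upper end and the boundary of 0.2, taken to be in dioptres, as a yardstick.

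Assumptions not in the documents: a share w of one arm is affected (5% to 20%), progression r is linear at 0.3 to 0.8 D per year, and affected children progress at the average rate. With m months between the carried value and month 8:

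understatement of that arm's mean change = w × r × m/12

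| Value carried forward | w = 5%, r = 0.3 | w = 10%, r = 0.5 | w = 20%, r = 0.8 |
|---|---|---|---|
| Baseline (m = 8) | 0.010 D | 0.033 D | 0.107 D |
| Month 3 (m = 5) | 0.006 D | 0.021 D | 0.067 D |

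For example, 0.20 × 0.8 × 8/12 = 0.107 D and 0.05 × 0.3 × 5/12 = 0.006 D. As shares of the boundary these are 0.107/0.2 = 53% and 0.006/0.2 = 3%. Carrying the month-5 value (m = 3) gives less: 0.05 × 0.3 × 3/12 = 0.004 D up to 0.20 × 0.8 × 3/12 = 0.040 D.

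**5. Direction.** Carrying a value forward understates progression. In the lenses-only arm this makes controls look better and shrinks an acupuncture advantage; in the acupuncture arm it enlarges one. If both arms are affected, the bias is the difference between the two shifts. Faster progression among affected children would increase the figures; another drug that slows progression would reduce them.

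**The case against.** The strongest reply is that the plan does not discard these children. Their data are kept, researchers contact the guardians, and only enrolment in error or lack of treatment removes a case from efficacy analysis. This stands, and it rules out two stronger readings.

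- A reader might infer that these children vanish from the month-8 comparison, and might compute how far the control mean moves when the fastest progressors are deleted. That calculation describes a deletion that the plan does not make. The harm is a substituted value.
- A reader might infer that dropouts get one closing assessment and no more. The text gives no number. It may mean one assessment or all the remaining ones; the fault is that it does not say.

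A third reply is that a child who turns to a non-drug therapy can still become a dropout through breach of the trial plan. This also stands: the asymmetry holds for the withdrawal list, not necessarily for the protocol as a whole. But breach of the plan appears there as a common cause of dropping out, not as a rule.

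Finally, nothing in the documents shows that other drugs are started mainly when myopia worsens, or more often among controls. That is correct, so no direction can be asserted. The list of dropout causes does include lack of efficacy, which makes a link to outcome plausible.

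None of these replies supplies a sentence that keeps the children on the scheduled examinations.

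**Conclusion.** The point holds as a conflict between the withdrawal rule and the intention-to-treat principle. As written, a guardian's change of medicine or use of a prohibited drug ends participation regardless of willingness to be examined, the last result becomes final, and no section preserves the later visits. The children remain in the analysis with an earlier value in place of the true one.

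The bias can run either way. Its size rests on assumptions about frequency and progression that the documents do not give: roughly 0.006 to 0.11 D in the affected arm's mean month-8 change when the month-3 or baseline value is carried, against a boundary of 0.2. The top of that range is deliberately severe, because it assigns the whole 20% allowance, meant for all causes, to one cause in one arm and carries baseline forward. At the low end the effect is negligible. The mismatch between the drug-only trigger and the wider ban is a real inconsistency but secondary. The correction should be made because it is cheap and removes a bias that cannot be repaired once the readings have been missed.

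**What to change.** Reconcile the sections on withdrawal conditions, standards of dropout cases, dropout cases and recruitment strategies so that they treat prohibited treatment in the same way. State that:

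- use of any prohibited treatment, drug or non-drug, is recorded with its date and does not end outcome follow-up;
- these children keep the month-3, 5 and 8 examinations unless examination is refused, and completing the assessment items means those remaining visits;
- they are analysed as randomised in the full analysis set with the values actually measured, and are left out only of the per-protocol set.

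Whether study treatment continues after such use is a clinical matter for the investigators, and this change does not touch it.

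The cost is protocol wording. The examinations are already in Table 1, and follow-up examinations are free to subjects. Trial status reports six participants recruited, so most of the sample would fall under the new wording. The small downside is that the full-analysis-set estimate then includes the effect of other treatment; the per-protocol analysis, already planned, shows the result without those children.

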## Background

Myopia is becoming increasingly common and has become a worldwide public health issue
[1]. In the United States and Europe, the incidence of myopia is 20% to 50%
[2]; in Asian countries, such as mainland China, Taiwan, Hong Kong, and Singapore, the incidence of myopia is 60 to 80%
[3–5]. Over the past 50 to 60 years, the incidence of myopia in East and Southeast Asian countries has rapidly increased. Approximately 80 to 90% of urban adolescents in these countries have myopia on graduating from high school
[1]. Myopia often occurs between six and eight years of age, develops rapidly between 13 and 16 years of age, and stabilizes after 16 years of age
[6]. Treatment of myopia in modern medicine is mainly optometric, and includes the use of spectacles (single-vision lenses (SVLs) and progressive addition lenses
[7] and contact lenses
[8, 9]. Refractive surgeries include laser-assisted *in situ* keratectomy, photorefractive keratectomy
[10–12], and posterior chamber phakic intraocular lenses
[13]. However, while the most commonly used treatment method (optometric) can increase the best corrected visual acuity, optometric methods are unable to improve the uncorrected visual acuity. Surgery can help eliminate the need for glasses, but may lead to complications, as indicated by long-term follow-up studies
[13, 14]. There is also an age limit for performing such surgery, and it is considered as the last treatment choice for teenagers.

Acupuncture is highly valued in traditional Chinese medicine, and enjoys a favorable history of more than 2,500 years. Acupuncture has helped millions of patients around the world, and has been shown to be effective in clinical treatment. In 1980, the World Health Organization recommended acupuncture as an effective alternative therapy
[15]. Previous studies have confirmed that acupuncture, ear pins, or ear massage can help treat mild myopia (<-3.0 D)
[16]. There are published reports on the use of acupuncture in the treatment of adolescent myopia, but most studies use visual acuity as the primary outcome measure. Indeed, visual acuity, as determined by eye examination, is easily influenced by many external factors. Therefore, we have designed a randomized controlled trial based on the physiology and pathology of myopia. In addition to using distance visual acuity, diopter, and axial length (AL)
[17] as indices of clinical observation, indices such as ciliary body thickness
[18] and lens thickness

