### Standards of excluded and dropout cases

#### Standards of dropout cases

All participants have the right to terminate the clinical trial at any time. Subjects who do not complete the clinical trial will be considered dropout cases. The common causes of dropouts are as follows: adverse events, lack of efficacy, violation of the trial plan, lost to follow-up (including the subjects or their guardians who decided to terminate the treatment), and other reasons.

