### Primary outcome

The primary outcome in this trial will be diopter measurement
[21]. After mydriasis using cyclopentolate hydrochloride eye drops (15 ml; Alcon-Couvreur, Puurs, Belgium), a comprehensive refractometer (AOS-1,500; Nidek, Aichi, Japan) will be used to conduct objective optometry (computer optometry and retinoscopy), then subjective optometrics. Subjective optometrics will be divided into the following two parts: optometrics will be conducted on a single eye (the right eye followed by the left eye), and a bilateral eye balance examination. Subjective optometrics of a single eye will be divided into the following three stages: the initial maximum plus the maximum visual acuity (MPMVA) will be identified, Jackson cross cylindrical lenses will be used to determine the axial direction and degree of the cylindrical lens, and the MPMVA will be repeated. The results will be recorded after optometrics. When the pupils recover, a re-examination will be carried out (three days after the use of cyclopentolate hydrochloride eye drops). After re-examination, the glasses will be tried again. The degree of the glasses will be marked on the glass trial frame, to be chosen by the subjects based on subjective judgment. Finally, the diopter of the glasses and prescription glasses will be determined. The optometrist will not participate in other parts of the trial. The main time points for evaluation of clinical efficacy will be the first, third, and sixth months after two months of treatment.

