### Secondary outcomes

The secondary outcomes in this study will include distance visual acuity
[22], AL
[17], lens thickness
[18], and ciliary body thickness
[19]. These indices will be measured before treatment, and at the first, third, and sixth months after two months of treatment. The objective examinations will be recorded in the CRFs. The main time points of evaluation will be the sixth month after treatment or when the trial is terminated.

Distance visual acuity will be measured using a standard logarithmic visual acuity test chart (TR-B; Tongrui Medical Equipment Co., Ltd., Tianjin, China), under sufficient lighting to measure the parameters of visual acuity, with a 5-m distance to the visual acuity test chart. All visual acuity examinations in this study will be carried out by one nurse in a fixed place who will not participate in acupuncture treatment or clinical examinations. The specific details of the subjects will not be disclosed to the nurse.

In order to measure AL and lens thicknesses, the subject will be placed in the supine position. Oxybuprocaine Hydrochloride Eye Drops (20 ml, Santen Pharmaceutical Co. Ltd. Suzhou, China) will be applied to the eye to be examined, and topical anesthesia will be applied. The subjects will be asked to watch the red light at the top of the probe with the eye to be examined. A disinfected ultrasound probe will be placed on the surface of the cornea. Sound waves will pass through the middle of the corneal vertex, the center of the lens, and the vitreous body, to reach the macular fovea. The sound beam will be kept in a vertical orientation. The AL and lens thicknesses will be measured. Ten sets of values will be selected, with a measurement error within 0.1 mm
[22]. The lens thickness is the axial distance from the front surface to the posterior surface of the lens
[19, 23]. An ophthalmic ultrasound instrument (CINESCAN; Quantal Medical, Paris, France) will be used for these measurements in the proposed study. Ten measurements of a particular index will usually be made, and these 10 measurements will be recorded and the average value obtained. The AL and lens thickness measurements will be carried out by one full-time physician, on a fixed instrument, and at a fixed location. The physician will not participate in visual acuity examinations and acupuncture treatment, and the specific details with respect to the grouping of subjects will not be disclosed to the physician.

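### Taking a withdrawn child's last result as the final result understates later myopia progression and can bias the month-8 comparison when the arms lose children in different numbers or at different times

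*Protocol article*

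**What the plan says.** The rule stands in Withdrawal conditions, in the passage on withdrawn cases: "The results of the last trial will be considered to be the final results". The wording is loose, but its natural meaning there is that the last recorded examination stands in for the final one.

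The same section lists among the reasons for withdrawal "if deterioration occurs during the trial and, based on the judgment of the physician, the trial should be terminated", and also the use of prohibited drugs. Standards of dropout cases adds: "The common causes of dropouts are as follows: adverse events, lack of efficacy, violation of the trial plan, lost to follow-up".

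For dropouts, the Dropout cases section says that "the researchers will contact the guardians and complete the assessment items" and that "The observational data on all dropout cases will be preserved for statistical analysis at the end of the trial". It does not say which items are completed, or that the child is examined again at the later visits.

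Table 1 places diopter at baseline and at months 3, 5 and 8, with nothing during the treatment phase. For the primary outcome the times are fixed: "The main time points for evaluation of clinical efficacy will be the first, third, and sixth months after two months of treatment". For the secondary outcomes an alternative is allowed: "The main time points of evaluation will be the sixth month after treatment or when the trial is terminated".

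Statistical analysis names intention-to-treat with full-analysis and per-protocol sets but does not replace the carry-forward rule. Table 2 leaves the method for diopter open between a t-test, a rank-sum test and an unspecified repeated-measurement analysis.

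**The concern.** Carrying a value forward does little harm when the outcome is stable. Here the article expects change: Background describes myopia as developing through childhood and adolescence and settling only after 16, and Table 2 frames benefit as axial length not growing. A value taken early is then a favourable value.

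Three features of the design make this matter. Reasons for leaving include deterioration and lack of efficacy, so missingness may depend on outcome. The burden differs by arm: 6 cycles of 9 daily sessions, or 54 sessions (Intervention), for which families pay half price (Recruitment strategies), against lenses only. And with no diopter between baseline and month 3, a child who leaves during treatment may have nothing but the baseline value to carry.

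At stake is whether the month-8 difference in diopter reflects treatment or partly reflects who left and when. The clause for secondary outcomes adds a second problem: it puts different lengths of follow-up into one endpoint.

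**Working it through.** **The plan's own figures.** The plan gives no figure for the effect of carry-forward. The only yardstick is in Sample size: S = 0.25, margin 0.2, θ printed as 3.0, normal deviates 1.645 and 0.845, n = 79, 20% dropout, 100 in total. The formula itself is not shown in the text at hand; the usual one for superiority by a margin is n per group = 2 × [S × (1.645 + 0.845) / (θ − 0.2)]².

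- θ = 3.0 as printed: 2 × (0.6225 / 2.8)² = 0.1, so 1 per group. This does not give 79.
- θ = 0.3: 2 × (0.6225 / 0.1)² = 77.5, so 78 per group, close to 79.

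So an excess over the margin of 0.3 − 0.2 = 0.1 D can be used as a yardstick only if 3.0 is meant as 0.3. That is an inference from n = 79; the protocol does not state it.

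**Inputs for the bias.** From the documents: final diopter at month 8, earlier diopters at baseline and months 3 and 5 (Table 1), 1:1 allocation, 20% dropout overall (Sample size). Assumed, because the documents do not give them: progression g of 0.25, 0.5 or 1.0 D/year, linear and equal in both arms; no true effect; dropout split 30%/10% or 25%/15%, each averaging 20%.

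**Formula.** A child whose last diopter is at month L is credited with g × (8 − L)/12 too little progression. With fractions d₁ and d₂ lost in the two arms, the false advantage of the arm with more loss is (d₁ − d₂) × g × (8 − L)/12.

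| g (D/year) | Loss by arm | Value carried | Progression left out (D) | Bias (D) |
|---|---|---|---|---|
| 0.25 | 30% v 10% | baseline | 0.25 × 8/12 = 0.167 | 0.20 × 0.167 = 0.033 |
| 0.5 | 30% v 10% | baseline | 0.5 × 8/12 = 0.333 | 0.20 × 0.333 = 0.067 |
| 1.0 | 30% v 10% | baseline | 1.0 × 8/12 = 0.667 | 0.20 × 0.667 = 0.133 |
| 0.5 | 30% v 10% | month 3 | 0.5 × 5/12 = 0.208 | 0.20 × 0.208 = 0.042 |
| 0.5 | 30% v 10% | month 5 | 0.5 × 3/12 = 0.125 | 0.20 × 0.125 = 0.025 |
| 0.5 | 25% v 15% | baseline | 0.333 | 0.10 × 0.333 = 0.033 |
| 0.5 | 25% v 15% | month 3 | 0.208 | 0.10 × 0.208 = 0.021 |
| 0.5 | 25% v 15% | month 5 | 0.125 | 0.10 × 0.125 = 0.013 |
| any | 20% v 20%, same times | any | equal in both arms | 0 |

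**Equal numbers, different timing.** If 20% leave in each arm, with baseline carried in one and month 5 in the other, the bias is 0.20 × g × (8 − 3)/12 = 0.021, 0.042 and 0.083 D at 0.25, 0.5 and 1.0 D/year.

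**Equal loss with a real effect.** If 20% in each arm carry baseline, those children contribute no difference, so an effect Δ is estimated as 0.80 × Δ.

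**Effect on the test, worst case only.** In a simulation of 20,000 trials (50 per arm, no true effect, 15 and 5 children set to zero change, SD of change taken as 0.25, one-sided 5% test against a zero difference), false positives were about 17%, 34% and 67% at the three rates. These figures do not apply if the 0.2 margin enters the test, which Statistical analysis does not make clear.

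**The case against.** The strongest reply is that the harm is conditional and partly mitigated. Much of this stands.

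- *A reader might infer that every child who leaves during treatment is scored at zero progression.* The documents do not support that. Staff are to contact guardians and complete the assessment items, which may yield an exit value, and Excluded cases removes children with a lack of treatment from the efficacy analysis. Baseline carry-forward is therefore the worst case. However, no later examinations of these children are scheduled, and some withdrawn children by definition no longer accept examinations.
- *A reader might infer that the rule favours acupuncture.* The heavier schedule makes more loss there plausible, but lack of efficacy or a turn to prohibited treatment could be commoner among unblinded lens-only controls, and the bias would then favour control. The documents give no dropout by arm.
- *Deterioration is undefined* and need not mean myopia progression. A child examined on leaving for that reason carries the worse value, and only later change is frozen.
- *The progression rate is outside the documents.* Background places the rapid phase at 13 to 16, while the trial enrols ages 7 to 12. The range therefore starts at 0.25 D/year.
- *The termination clause concerns secondary outcomes only.* A reader might extend it to diopter, but Primary outcome has fixed times and no such clause.
- *A separate analysis plan may handle missing data.* It may, but this article does not merely leave the matter open: it states a rule, and its intention-to-treat wording does not displace it.

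**Conclusion.** The point holds in conditional form. The protocol fixes carry-forward for an outcome it expects to worsen with time, and nothing in it secures equal loss at equal times. If myopia progresses during the 8 months, the arm with more or earlier loss gains a false advantage; with matched loss there is no bias under no effect, but the part of a real effect that arises after the carried visit is lost.

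The direction relative to the pattern of loss follows from the premise of progression; the size rests on assumed progression and dropout splits. It ranges from 0.013 D (25% v 15%, month 5 carried, 0.5 D/year) to 0.133 D (30% v 10%, baseline carried, 1.0 D/year).

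A reader might conclude that dropout alone could match or exceed the planned excess over the margin. That comparison needs θ to be 0.3, so that the excess is 0.1 D; against the printed 3.0 the gap is 2.8 and the bias is small. The rule should be fixed, but the documents do not show that the result will be biased, or which arm would gain.

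**What to change.** 1. In Withdrawal conditions, delete the carry-forward sentence. The clinical criteria for withdrawal need no change for this purpose.
2. In Secondary outcomes, delete the alternative that allows evaluation at termination, so that every child is read at the same time point.
3. State in Dropout cases that withdrawn children continue to be invited to the month 3, 5 and 8 examinations, where guardians agree. Recruitment strategies already makes follow-up examinations free, and staff already contact guardians.
4. In Table 2, specify the repeated-measurement option for diopter as a likelihood-based model of all observed visits, with arm by visit and baseline diopter, and name the month-8 contrast as the one to be read. Table 2 does not say this now.
5. Add a tipping-point analysis that shifts the unobserved values of dropouts, by arm, until the conclusion changes. This is needed because the model assumes data missing at random, while withdrawal may depend on outcome.

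The cost is a little more programming and follow-up contact. Trial status reports six participants recruited, so at that stage the change could be made before most outcome data exist.
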